All compounds in hotspots will be visited in March 2012, and children between 6 months and 20 years of age will be tested for malaria parasites using a rapid diagnostic test based on the detection of malaria antigens (Premier Medical First Response Combo^®^,) using one of the best tests in a recent evaluation of the World Health Organization [18]. This test is based on the detection of *P. falciparum* specific histidine rich protein-2 (HRP-2) and Lactate dehydrogenase (LDH) and thereby circumvents problems of false-positivity common to HRP-2 based tests. If a single individual in this age group is found positive by RDT every individual within this compound will be treated with AL except for pregnant females. For these individuals transport will be provided to a health facility in the area and costs covered for examinations and government recommended anti-malarial treatments. Children under the age of 6 months will not be treated. A second round of FSAT is planned for September 2012.

Consent will be obtained separately for each intervention at the DOMC, administrative and community level (all interventions), the compound level (IRS and LLINs), or the individual level (FSAT). In the case of permanent breeding sites that are privately owned (e.g. fish ponds) verbal consent will be sought from community and owners before larviciding takes place. Other studies have shown no negative impact of larviciding using *Bacillus thuringiensis var. israelensis* on fish population and acceptance of larviciding by fish pond owners and the community ([name] *pers comm.*).

The other clusters will serve as control areas; hotspots in these areas will not be targeted.

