During a second visit, one month after initial LLIN distribution the correct usage of LLINs will be evaluated: the correct hanging of LLINs will be confirmed and household members will be asked to explain how they use the net. If needed, instructions about correct use will be repeated and additional nets can be provided if nets are missing or found to be torn. A third visit will occur to re-assess the quality and use of the nets 6 months after the first visit, in conjunction with the second round of IRS. At this point new ownership and quality will be re-assessed and new nets will be distributed as needed. All information on net use and quality will be recorded (appendix D).

*Focal Screening and Treatment (FSAT)*

Screening of a sentinel population within households

The FSAT utilizes individuals aged 6 month to 20 years as a sentinel group to indicate malaria exposure in the household because this age-group experiences the highest parasite burden [23-24]. For this age group all individuals will be tested for parasites using RDTs regardless of presence of symptoms or not. However clinical care will not be restricted to just this age group. All age groups may experience clinical malaria in our setting ([name] *et al.*, in preparation) and therefore those individuals over 20 years who are found to have fever will also be tested by RDT and receive treatment as oart of the FSAT intervention.

The FSAT campaign will take place in intervention hotspots in March 2012; a second round of FSAT is planned to take place in September 2012. Both campaigns will follow identical procedures.

Screening the sentinel group

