Treatment will be carried out using artemether-lumefantrine (Coartem, AL) according to national guidelines. AL is an antimalarial drug with an excellent safety profile; limited data on safety are available for children under 6 months and pregnant women, both groups will therefore be excluded from AL treatment (see below) but receive clinical care when necessary. As detailed below, all those who are given Coartem will be actively followed-up to monitor any side effects. This monitoring will happen on all days of treatment and one week after the start of treatment. If given to parasite-free individuals, AL will provide an effective prophylactic effect for 3-4 weeks, which has been shown to be highly beneficial for malaria control purposes in high endemic regions [36]. In parasite carriers, AL effectively clears asexual parasites and gametocytes, the parasite stage responsible for transmission [35]; the timing of FSAT is chosen to ensure individuals are parasite and gametocyte-free before the start of the peak transmission season. For those receiving AL, the first dose will be supervised and then instructions will be provided for taking of the second dose which will be issued. Teams will return to compounds the next day to administer and supervise the third dose and distribute the fourth. They will return again on the third treatment day to again administer and supervise the fifth dose and distribute the sixth. At the same time any side effects will be noted. (see appendix G & H).

All participants will be told their haemoglobin level immediately, and any person found to be anaemic will be provided haematinics according to national guidelines.

Treatment of risk groups: children <6 months and pregnant women

Children below 6 months of age will be excluded from the study; they will be screened for fever and referred to a health facility where needed but will not be included in FSAT.

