Pregnant women will not receive AL. Prior to consent and treatment, it will be explained why AL cannot be given to pregnant women and therefore the necessity to assess whether women of childbearing age may be pregnant if anyone in their household is found to be positive for malaria. Women may opt not to be tested for malaria. In each survey team there will be a female field worker trained to carry out interviews and test for pregnancy. She will approach women of childbearing age (13-45 years) in households where there is ≥1 parasite positive participant. These women will be asked whether they could be pregnant, and the date of their last menstrual period. Women whose last menstrual period was not within the prior 4 weeks, and/or who could be pregnant will be asked whether they would be willing to perform a pregnancy test on their urine sample. A recent survey of houses in the study area showed all to have pit latrines where a urine sample can be collected and a pregnancy test can then be conducted by the field worker away from the house. Women will be provided results of their pregnancy test in a private area in a confidential manner. This was shown to work in a sister study (SSC 1517). Confidentiality will be ensured at all times. Females whom have a negative pregnancy test can be given AL.

Women with a positive pregnancy test or those who would rather not have a pregnancy test performed will be offered a test for malaria parasites by RDT. If a woman who is pregnant or may be pregnant is parasite positive by RDT, she will be offered to be taken to a nearby health facility for examination and appropriate treatment before being returned home. If a women who is pregnant or may be pregnant is parasite negative by RDT, she will be asked about her last dose of intermittent preventive treatment in pregnancy (IPTp) with sulphadoxine-pyrimethamine (SP) and her antenatal records will be consulted. If the IPTp dose of SP was given <4 weeks ago, no additional treatment will be given. If the dose is >4 weeks ago or a woman has never received IPTp and the woman is eligible for a dose of SP according to national guidelines, she will be offered to be taken to a nearby health facility for examination and appropriate treatment before being returned home. All costs incurred by the woman will be covered by the project.

As part of the supervisory team a qualified Clinical Officer will be available to advise on all treatment regimes and any side effects from drugs taken.

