c. Risks to intervention participants

None of the interventions that are proposed in this study are experimental. LLINs and IRS are part of the malaria control efforts by the DOMC for the district; larviciding has been done in districts bordering or close to Rachuonyo district, in Nyando, Kisii, Suba and Kakamega districts [22]. All insecticides used will have been approved by DOMC and PCPB prior to application. The FSAT approach to screen asymptomatic children and treat all inhabitants of households where ≥1 individual is found parasite positive by RDT has not been done routinely in Kenya but is an extension of screening and treatment of asymptomatic individuals that is proposed under the Kenyan National Malaria Strategy for 2009-2017[[13](#_ENREF_13)]. The national strategy does not currently propose to treat household members of asymptomatic parasite carriers; the approach is justified by evidence of clustering of parasite carriage at household level [2, 6, 25, 33] and the low sensitivity of RDTs for detecting all epidemiologically relevant parasite densities [[14](#_ENREF_14)]. We will provide supervised treatment with the first line antimalarial drug AL that has an excellent safety profile and is recommended for treatment of symptomatic and asymptomatic malaria infections in Kenya [[13](#_ENREF_13)]. We will also closely monitor and document any reported side effects of all interventions by questionnaires on all days of treatment and one week after treatment, IRS and ITN distribution.

d. Benefits to survey participants

All participants of the cross-sectional survey will benefit from knowing their haemoglobin level and whether they have a clinical malaria infection. Any participant with low haemoglobin will receive treatment for anaemia. All individuals who are diagnosed with a clinical malaria episode will be treated with AL according to Kenya national guidelines.

e. Risks to survey participants

This survey is of minimal risk to participants. Blood will be collected by fingerprick only using a sterile lancet, and the total amount of blood collected is very small (200-300μl); participants may experience only a small bruise at the site where we collect the blood. Blood draws will be carried out by trained medical or laboratory staff members to ensure these are done in as safe a manner as possible.

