After screening, each person who is diagnosed with clinical malaria will be treated with first line malaria treatment recommended by the Ministry of Health, Kenya, AL. AL is considered a very safe drug except in pregnant women (where there may be possible risk to the developing foetus) and very young children (where safety data to support its use are not available).

To minimize drug exposure in these risk groups, children under 6 months of age will be excluded from the study, and pregnant women will receive alternative medication as outlined above.

We will take steps to ensure that each study participant’s personal information will be protected. All questionnaires will be labelled with the participant name and person ID. Filter paper samples and other samples will be labelled using a personal ID only, which will only be known to study staff. After the questionnaires are completed, they will be returned to the data management staff while the filter paper samples will be returned to the laboratory staff at KEMRI/CDC in Kisian. Once at the laboratory, only data management staff will possess the link between the laboratory samples and the participants’ identifiable information.

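### The adverse event forms do not name pregnancy loss, stillbirth or congenital anomaly, although some early pregnancies can still be exposed to artemether-lumefantrine (minor; descriptive safety only)

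*Protocol*

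**What the plan says.** **Foetal risk.** Section 12e, on risks to survey participants, states: "AL is considered a very safe drug except in pregnant women (where there may be possible risk to the developing foetus". Section 9f separately excludes pregnant women from AL under focal screening and treatment (FSAT) because safety data in them are limited.

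**Screening before AL.** In households with a positive member, women aged 13 to 45 are approached: "parasite positive participant. These women will be asked whether they could be pregnant, and the date of their last menstrual period". A urine test is then offered selectively: "Women whose last menstrual period was not within the prior 4 weeks, and/or who could be pregnant will be asked" whether they are willing to test. Women who test positive or decline the test get no AL. Women who test negative can be given it, and no repeat test is stated.

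**Follow-up after AL.** Section 9f: "This monitoring will happen on all days of treatment and one week after the start of treatment". Section 12c puts it slightly differently: "by questionnaires on all days of treatment and one week after treatment, IRS and ITN distribution". Either way, active follow-up ends at about one week.

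**Forms.** The FSAT checklist in Appendix G has 11 items, the last being free text, and none concerns pregnancy. It sends an event to the SAE form when the event is severe or life-threatening. Form H1 lists death, threat to life, hospitalisation, disability, and intervention to prevent a serious outcome. The SAE tick list repeats these and adds a free-text Other. H1 also has a Day 42 field for the date on which an event resolved.

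**The concern.** The protocol treats foetal exposure as the reason to withhold AL, yet the forms meant to record serious harm do not name the outcomes in which such harm would appear. A pregnancy loss managed at home without treatment meets none of H1's printed criteria. The symptom grading tables in Appendix H have no entry for it either, so the severity trigger in Appendix G gives field staff nothing to apply. A birth defect that is not disabling, hospitalised or treated is in the same position.

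This matters somewhat more here than in ordinary case management. Section 9f gives AL to household members of a positive person, and accepts that some of them carry no detectable parasites. The stake is completeness of descriptive safety reporting: how many pregnancies were exposed and how they ended.

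**Working it through.** The protocol gives no figure to reproduce. The check has two parts: who can be exposed, and when an outcome could be seen.

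**1. Routes of exposure that remain**
- FSAT, untested: last period within 4 weeks, possible pregnancy not reported, so no test is requested.
- FSAT, tested: a pregnancy too early for the urine test; a negative result permits AL.
- Surveys: Section 9g treats febrile participants with a positive rapid test at home, in both arms, with the same precautions for women of childbearing age.

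**2. Timing**

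Assumptions, not taken from the protocol: term is 40 weeks from last period. For the untested route, last period was 0 to 4 weeks before AL, so term birth falls 36 to 40 weeks (252 to 280 days) after dosing.

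- One-week check: 0 + 1 to 4 + 1 = 1 to 5 weeks from last period. Women dosed at 0 to 3 weeks are then at 1 to 4 weeks, still a recent period under the protocol's own 4-week rule, so the check would not reveal the pregnancy.
- Day 42: 0 + 6 to 4 + 6 = 6 to 10 weeks from last period. Delivery is still 252 − 42 = 210 to 280 − 42 = 238 days away, or 30 to 34 weeks.
- March 2012 dosing, seen in September 2012: the shortest gap is 31 March to 1 September, 154 days = 22.0 weeks; the longest is 1 March to 30 September, 213 days = 30.4 weeks. Adding 0 to 4 weeks gives 22.0 to 34.4 weeks from last period. A continuing pregnancy is undelivered at term; an earlier loss has already happened.
- Term births after March 2012 dosing: 1 March + 252 days = 8 November 2012, to 31 March + 280 days = 5 January 2013. The last is 55 days before 1 March 2013.
- September 2012 dosing, seen in March 2013: 152 to 211 days, or 21.7 to 30.1 weeks; adding 0 to 4 gives 21.7 to 34.1 weeks.
- Term births after September 2012 dosing: 1 September + 252 days = 11 May 2013, to 30 September + 280 days = 7 July 2013, all after March 2013.
- Test-negative route: the last period may lie further back, so births come earlier. To deliver at term by 31 March 2013, a woman dosed on 1 September 2012 would have to have been at least 40 − 30.1 = 9.9 weeks from last period when she tested negative.

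**3. What the planned contacts would pick up**

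Section 9f says of the March and September 2012 rounds: "Both campaigns will follow identical procedures". The September round therefore repeats the pregnancy questions, but only in households positive at that round. It does not ask about losses or link back to the earlier AL. Census updates would list a surviving infant, but the Appendix C form has no field for the mother, a loss or an anomaly.

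**4. What questions at later FSAT rounds would cover**

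Term births from 1 of the 2 rounds in 2012 if a March 2013 round is held, and from 0 of 2 if it is not. Losses between rounds could be asked about after the March 2012 round in either case, and after the September 2012 round only if March 2013 is held.

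**The case against.** The case against is that the protocol states nothing false here. Screening is careful, a loss that is hospitalised or treated already meets a printed criterion, and free-text lines exist on both the checklist and the SAE form. Follow-up is active in the first week, compounds are revisited one month after net distribution, and a Clinical Officer advises on side effects. The consent and information appendices are not available for review and may tell women to report a pregnancy. A question six months later relies on recall, intrudes on many women to find a few, and cannot reach births after the September 2012 round.

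Most of this stands. It is why capture is partial rather than absent, and why the point is minor. It does not remove the gap: free text depends on someone volunteering the event, the one-month visit concerns nets, and a self-report instruction would leave the printed criteria unchanged.

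Three stronger readings are tempting and unsupported. A reader might infer that pregnant women will knowingly be given AL; Section 9f excludes them and those who decline the test. A reader might infer that pregnancy outcomes go wholly unrecorded; the generic criteria and free text contradict that. A reader might also infer that better capture would show or exclude foetal harm. The documents give no count of exposed women, numbers are likely to be too small, and FSAT is given only in intervention hotspots, so its counts have no control comparison.

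**Conclusion.** The point holds as a minor, inexpensive improvement to descriptive safety recording. The omission from both forms is plain on the page, and at least two FSAT routes, plus treatment in the surveys, leave early pregnancies open to exposure. Active monitoring ends at about one week, and the Day 42 field, which concerns event resolution, falls 30 to 34 weeks short of term birth for women exposed untested.

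The timing rests on the assumed 40-week term and a last period 0 to 4 weeks before dosing. The number of exposed pregnancies cannot be derived from the protocol and none is claimed. That capture beyond the first week is otherwise passive is subject to the unseen appendices. Nothing here touches the primary outcome, randomisation or power, and nothing calls for a change in who receives AL.

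**What to change.** 1. Add *pregnancy loss, stillbirth or congenital anomaly* to the H1 seriousness criteria and to the SAE tick list, so that such an event goes to the SAE form whatever its severity grade.

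2. Keep a confidential list of women aged 13 to 45 given AL under FSAT. At the September 2012 round, and at a March 2013 round if held, ask each woman treated at the previous round, in private, whether she was pregnant at or soon after treatment and what the outcome was. Ask whether or not her household is positive at that round. The staff exist: "In each survey team there will be a female field worker trained to carry out interviews and test for pregnancy". The compounds are already on the route: Section 9d says "All compounds in hotspots will be visited in March 2012", and the September round follows the same procedures.

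3. Report the counts descriptively, including ongoing and not traced, with no test. State that women treated only in surveys, and births after the September 2012 round (about May to July 2013) or after any March 2013 round, are not systematically captured.

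**Cost.** One line on each of two forms, the list, a few minutes per woman, some privacy burden, and possibly a line of consent wording. Recall reaches back about six months and women who move away are missed. The March 2013 step is uncertain: Section 11 dates FSAT to March 2012/2013, while Section 9f makes later roll-out depend on first-year results. No extra staff are needed for these steps.

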## g. Procedures: evaluation phase

**Community cross-sectional surveys**

*Consent procedure cross-sectional surveys:*

As with the intervention phase, meetings will be organised with the district commissioner, officers and chiefs with the district health team to seek approval for the evaluation phase. Sensitization of communities will be done by chiefs and assistant chiefs and village elders from the study area. Community meetings (barazas) will be held in the selected areas and study staff will explain the purpose of the surveys, the procedures to be followed and the risks and benefits of participation. Information sheets shall be provided in English, DhoLuo, or Kiswahili to all district representatives, chiefs and households (Appendix A).

Households will be informed at the barazas of the timing of the survey and that their compounds may be visited.

On the day of the cross-sectional survey informed consent will be obtained at the individual level. All consent forms will be available in English, DhoLuo, or Kiswahili. Translations will be checked through back-translation (Appendix B). Consent will be obtained by signature or thumb-print accompanied by the signature of an independent witness of selected individuals and/or their parents/guardians. Assent forms will be signed by children between the ages of 13 and 17 years and by their parents/guardians. Each assent form will be accompanied by consent form signed by the parent/guardian.

*Timing of the cross-sectional surveys:*

Six cross-sectional surveys will be conducted (see table in section 11):

- Pre-transmission season (March 2012)
- Peak transmission season (June 2012)
- Post transmission season (September 2012)
- Pre-transmission season (March 2013)
- Peak transmission season (June 2013)
- Post transmission season (September 2013; final survey)

*Procedure cross-sectional surveys:*

Prior to the surveys, census lists for all hotspots will be updated using PDAs, recording the name, age and gender of each household occupant (see appendix C for summary of information collected). For each cross-sectional survey up to 100 individuals above the age of 6 months will be randomly selected from malaria hotspots and up to 500 participants above the age of 6 months will be randomly selected from outside malaria hotspots in each cluster. Randomization will occur at the compound level.

Each occupied house in the randomly selected compounds will be visited by a team of fieldworkers. The head of the house will then be interviewed using a personalized digital assistant (PDA) to record information. The interview will assess household construction, wealth indices and use of anti-malarial measures (recent IRS activities, bednet ownership and use, use of mosquito coils, sprays etc.). Each selected participant or their parent/guardian will be interviewed inquiring about recent fever episodes, treatment seeking behaviour, ITN use and travel history. The transcript of the questionnaire is given in Appendix E. On the PDA translations for questions will be available by pressing buttons for DhoLuo or Kiswahili. The questionnaire it will be broken down into 4 parts; the first records details of the household, the second logs bednets, the third records personal details and the last records results of tests completed.

Temperature will be measured by ear thermometer; a single fingerprick blood sample will be used to i) determine haemoglobin levels using a Copack Haemoglobin Colour Scale system (blood sample spotted onto a special filter paper), ii) prepare a microscopy slide (sample taken directly from the finger onto a slide) and iii) collect a blood sample into an EDTA microtainer tube and onto a filter paper for parasite PCR and the detection of malaria-specific antibody responses by ELISA. For all individuals with fever (≥37.5°C), the presence of malaria parasites will be determined immediately by rapid diagnostic test (RDT, directly from the finger). Anyone with fever and a positive RDT will be treated for malaria at the home according to national guidelines (see above for procedures women of childbearing age). All participants will be told their haemoglobin level immediately, and any person found to be anaemic will be provided haematinics according to national guidelines. The volume of the blood sample taken for all measurements combined will be 200-300μL.

